## Abstract

**Background:**

It is estimated that seniors (≥65 years old) account for >50 % of acute inpatient hospital days and are presenting for surgical evaluation of acute illness in increasing numbers. Unfortunately, conventional acute care models rarely take into account needs of the elderly population. The failure to consider these special needs have resulted in poor outcomes, longer lengths of hospital stay and have likely increased the need for institutional care. Acute Care for the Elderly models on medical wards have demonstrated decreased cost, length of hospital stay, readmissions and improved cognition, function and patient/staff satisfaction. We hypothesize that specific Elder-friendly Approaches to the Surgical Environment (EASE) interventions will similarly improve health outcomes in a cost-effective manner.

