### Aim & objectives

The aim of the EASE study is to assess the impact of an elder-friendly surgical unit, with the goal of delivering evidence-informed care to improve the quality of care to older acute surgical patients, in order to reduce unnecessary health care resource utilization. The EASE study will realign current resources, implement evidence-informed practices, and improve health outcomes in a cost-effective manner.

The specific objectives of the EASE Study are to:Assess the clinical effectiveness of the EASE initiatives in reducing the rate of post-surgical complications, in-hospital mortality and length of stay, compared to controls.Determine if the EASE initiatives improves humanistic outcomes including health-related quality of life (HRQL), functional capacity and patient satisfaction, compared to controls.Determine the incremental cost and cost-effectiveness of the EASE initiatives.

In aggregate, these objectives will assess the program’s impact on a comprehensive range of outcomes important to patients, providers, and policy-makers.

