For cost analysis, exploratory baseline analyses will be completed including calculation of mean index hospitalization cost, median index hospitalization cost, mean readmission cost, median readmission cost and measures of central tendency for both variables. The cost of the intervention will also be calculated and included in the total cost post-EASE. All costs pre-EASE and post-EASE will be compared between sites. The difference in costs between sites will be calculated and compared. If required, a risk-adjustment model to predict cost differences between sites will be developed. A cost per quality adjusted life year (QALY) gained will also be calculated. The mean cost difference in each site will be divided by the QALYs achieved in each site. QALYs will be calculated using the utility values measured by the EQ-5D and the length of life of each patient.

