## Discussion

In summary, EASE is a prospective, before-after study with a concurrent control group. EASE aims to assess the impact of an elder-friendly surgical unit with the goal of delivering evidence-informed care to improve the quality of care to older acute surgical patients and result in optimal use of health care resources.

Given the current aging population and the rising burden of chronic disease and frailty, new patient-centred, comprehensive and interdisciplinary models of Acute Care Surgery are needed to optimize care in this vulnerable patient population. This proposed research will generate new knowledge on acute surgical outcomes in older patients and validate the novel model of care, including assessment of the associated economic benefits. If effective, we expect the EASE initiatives to be generalizable to other surgical centers.

EASE commenced enrolment in April 2014. Recruitment of all pre-EASE subjects is expected by spring 2015, with implementation of the EASE initiatives in summer 2015. Completion of all post-EASE subject recruitment is expected to take until mid-2016, with final study results anticipated in late 2016.

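### The cost-per-QALY summary is defined inconsistently (QALYs gained versus QALYs achieved), and even a corrected ratio is hard to interpret if costs fall

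*Protocol article*

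**What the plan says.** The third objective under Aim & objectives is the incremental cost and cost-effectiveness of EASE. The cost paragraph of Data analysis sets out the following:

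- The statistic: "A cost per quality adjusted life year (QALY) gained will also be calculated".
- Its formula: "The mean cost difference in each site will be divided by the QALYs achieved in each site".
- The QALYs: "QALYs will be calculated using the utility values measured by the EQ-5D and the length of life of each patient".
- The cost comparison, reported on its own: "The difference in costs between sites will be calculated and compared".
- The programme's own cost: "The cost of the intervention will also be calculated and included in the total cost post-EASE".

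No other cost-effectiveness summary is named.

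On direction, the study aim is to improve care "in order to reduce unnecessary health care resource utilization". The abstract cites a precedent: "Acute Care for the Elderly models on medical wards have demonstrated decreased cost, length of hospital stay, readmissions". The Discussion hopes to "validate the novel model of care, including assessment of the associated economic benefits". The hypothesis itself speaks of cost-effectiveness, not of savings.

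**The concern.** There are two linked problems.

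1. **The statistic and its formula disagree.** A cost per QALY gained needs a QALY difference in the denominator. The formula uses the QALYs accrued in a site. It also yields one ratio per site, including one for the control site, which receives no intervention. The rest of Data analysis is built on the between-site difference of pre-post differences, and two site-specific ratios cannot be turned into the ratio of those differences.

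2. **Correcting the denominator exposes a weakness of the ratio itself.** If EASE reduces cost, the incremental ratio is negative when QALYs rise. Negative ratios have no valid ordering. When the QALY difference is small relative to its error, the denominator can fall on either side of zero and an ordinary confidence interval for the ratio is not available.

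At stake is what the third objective can conclude. The primary clinical outcome is not affected.

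**Working it through.** The document gives no expected cost, QALY difference or threshold, so there is no planned figure to reproduce. **Assumed inputs:** cost difference dC = ±$2,000; QALY difference dQ = ±0.02; 0.35 QALY achieved over six months (range 0.25 to 0.45); willingness to pay $50,000 per QALY (range 0 to $100,000).

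**Step 1. The formula as written: dC / QALYs achieved.** For simplicity the control site's cost is unchanged.

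| Result | Calculation | Ratio |
|---|---|---|
| Cheaper, better | -2,000 / 0.37 | -5,405 |
| Cheaper, worse | -2,000 / 0.33 | -6,061 |
| Dearer, no QALY change | 2,000 / 0.35 | +5,714 |
| Dearer, better | 2,000 / 0.37 | +5,405 |
| Dearer, worse | 2,000 / 0.33 | +6,061 |

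- The sign follows cost alone, because the denominator is in practice always positive.
- For a fixed saving, the worse health result looks more favourable (-6,061 against -5,405). This holds for any positive level: at 0.25 achieved the pair is -8,696 and -7,407; at 0.45 it is -4,651 and -4,255.
- The dearer-and-better case has a true incremental ratio of 2,000 / 0.02 = 100,000. The written formula shows 5,405, smaller by a factor of 0.37 / 0.02 = 18.5.
- All three dearer results lie far below $50,000, including the one that loses health.

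**Step 2. A corrected incremental ratio, dC / dQ, beside net monetary benefit, NMB = willingness to pay × dQ - dC.**

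| Result | dC | dQ | Ratio | NMB at 50,000 | NMB, 0 to 100,000 |
|---|---|---|---|---|---|
| Cheaper, better | -2,000 | +0.02 | -100,000 | +3,000 | +2,000 to +4,000 |
| Cheaper, better still | -2,000 | +0.04 | -50,000 | +4,000 | +2,000 to +6,000 |
| Both twice as large | -4,000 | +0.04 | -100,000 | +6,000 | +4,000 to +8,000 |
| Dearer, worse | +2,000 | -0.02 | -100,000 | -3,000 | -2,000 to -4,000 |

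Three different results share -100,000, and doubling only the health gain moves the ratio towards zero. NMB separates best from worst at every threshold.

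**Step 3. Can the denominator cross zero?** The standard error of a four-cohort contrast is SD × √(4/n), with n per cohort. The planned n is 140. I also take 70, because Sample size calculation anticipates high attrition at follow-up and EQ-5D is collected only at 6 weeks and 6 months. With an assumed true gain of 0.02:

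| QALY SD | n | SE | Chance the estimated difference is negative |
|---|---|---|---|
| 0.10 | 140 | 0.0169 | 12% |
| 0.10 | 70 | 0.0239 | 20% |
| 0.12 | 140 | 0.0203 | 16% |
| 0.12 | 70 | 0.0287 | 24% |

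At SD 0.12 and n = 140, a true gain of 0.01 makes this 31%, and 0.04 makes it 2%.

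Now add a true saving of $2,000 with independent errors, at n = 140. With QALY SD 0.10 and a cost standard error of $2,500, the estimate is cheaper-and-better in 69% of trials and dearer-and-worse in 3%. With SD 0.12 and $4,000 these are 58% and 5%. The remaining 28% and 37% give a positive ratio, which itself mixes dearer-and-better with cheaper-and-worse.

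**The case against.** The strongest reply has four parts.

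- **The best/worst collision does not arise under the written formula.** This is correct. The denominator is positive, so cheaper-and-better and dearer-and-worse have opposite signs (-5,405 and +6,061). A reader might infer that the plan as written cannot tell its best result from its worst; the text does not support that. The collision belongs to the corrected ratio. The written formula fails differently, by not registering whether QALYs were gained.
- **Components are reported separately.** The cost difference is, and its sign read with an incremental ratio's sign identifies the quadrant of the point estimate. So it would be wrong to say the third objective rests on the ratio alone. This does not repair the ordering or supply an interval. Quality of life is a secondary outcome analysed as a difference of differences, but no incremental QALY difference is named.
- **Savings are not a stated expectation.** A reader might infer that the trial expects EASE to save money. The aim, the medical-ward precedent and the reference to economic benefits make savings plausible, but no section assumes them, and adding the programme's cost to the post-EASE total leaves the net sign open.
- **An article may leave net benefit and the handling of dominance to a fuller document.** This stands: their absence alone is no finding. The finding is that the one statistic and formula the article does fix are inconsistent.

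Net benefit also does not remove sampling noise. With SD 0.12 and a cost standard error of $4,000, its standard error at $50,000 is √((50,000 × 0.0203)² + 4,000²), about $4,127. The 95% interval around +$3,000 is then roughly -$5,100 to +$11,100. It is wide, but it can be interpreted.

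**Conclusion.** The point holds in two parts. The first is certain from the text: a cost per QALY gained is promised and a division by QALYs achieved is prescribed, and these are different quantities. In the illustration they differ by a factor of 18.5, and the written formula gives an apparently low price to a result with no health gain. The second is conditional. Once the formula is made incremental, the ratio is a poor summary if costs fall or if the QALY difference is near zero, and taken alone a negative value does not separate cheaper-and-better from dearer-and-worse.

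The ordering and sign faults do not depend on the assumed values. The dollar sizes and probabilities do, and are illustrative only. This is a cheap improvement to a secondary economic analysis.

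**What to change.** In the cost paragraph of Data analysis:

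1. Replace the formula. Define incremental cost and incremental QALYs each as the between-site difference of pre-post differences, and report both with 95% intervals.
2. Make incremental net monetary benefit the cost-effectiveness summary. For each patient compute willingness to pay × QALYs minus total cost, analyse it in the same site-by-period model as the other secondary outcomes, and give the estimate and 95% interval over a stated range of willingness-to-pay values.
3. Quote a cost per QALY only when both differences are positive. Otherwise state dominance or a trade-off.

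The cost is a few sentences and a short extra analysis of data already being collected. The downside is that a willingness-to-pay range has to be chosen and stated. Net benefit needs the same EQ-5D follow-up as the ratio, so it neither adds to nor cures the attrition problem.

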### Data collection

Study personnel will collect data using standardized case report forms recorded on an electronic database using a secure, internet-based portal.**Socio-demographic information (baseline)**: including age, sex, ethnicity, body mass index, medical comorbidities, residence prior to admission, blood pressure, heart rate, respiratory rate, haemoglobin, creatinine and medication history. Data obtained from chart review will be used to create the Charlson comorbidity index [43] and Rockwood’s frailty index [44].**Hospitalization details (baseline):** including admitting diagnosis, operative procedure, operating surgeon, American Society of Anaesthesiologists Class, requirements for alternative service consults, total parenteral nutrition and urinary catheter utilization, discharge location, and any new requirement for alternative level of care upon discharge.**Major in-hospital complications (baseline):** all complications are defined using the Centers for Disease Control definitions [45], including:Intensive care unit admission (includes respiratory failure, cardiac arrest or septic shock),Vascular complications (myocardial infarction, stroke, deep venous thrombosis, pulmonary embolism)Serious infections (pneumonia, intra-abdominal abscess, urinary tract infection, deep wound infection or infected decubitus ulcer), andProtracted delirium (≥48 h). A validated chart-based method for identification of delirium will be utilized [46]. This chart-based instrument has a sensitivity of 74 % and a specificity of 83 %, using the Confusion Assessment Method [47] as the gold standard.**Mortality (baseline, 6 weeks, 6 months):** divided into in-hospital mortality, 30-day mortality and 6 month mortality.**Length of hospital stay (baseline):** divided into:acute length of stay defined as time until the acute medical treatment for that patient is complete;total length of stay which includes both medical treatment time and time awaiting transfer to another hospital (e.g., rural hospital) or alternative level of care (assisted living, long-term care placement or rehabilitation).**Readmission (6 weeks, 6 months):** divided into 30-day readmission and 6 month readmission.**Functional status (6 weeks):** including:Edmonton Frail Scale [48]: a valid and reliable tool to assess the frailty of the older patients. The scale has 11 items assessing cognition, general health status, functional independence, social support, medication use, nutrition, mood, continence and functional performance. Higher scores indicate greater frailty.Timed Up and Go [49]: a commonly used screening tool for falls risk. The patient is timed while they rise from an arm chair, walk three metres at a comfortable and safe pace, turn and walk back to the chair and sit down again. Faster time indicates a better functional performance.**Cognitive status (6 weeks):** using the Abbreviated Mental Test Score [50]. This 10 item test screens older patients for possible cognitive impairment, with lower scores indicating greater impairment.**Quality of life and health status (6 weeks and 6 months):**EQ-5D [51]: A widely used, validated, preference based generic HRQL instrument. It encompasses five domains of HRQL (mobility, self-care, usual activities, pain/discomfort, and anxiety/depression) and a visual analogue scale. The five health domains can be scored and totalled to yield a single Index (EQ-Index) score anchored between 0 (death) and 1 (full health). The visual analogue scale ranges from 0 to 100 with higher scores indicating better HRQL. The EQ-5D is also a measure of utility; a requirement for cost-effectiveness analyses.SF-12 [52]: A widely used, validated, generic HRQL instrument. It yields a physical and a mental health component summary score. Higher scores indicate better health status.**Nutritional status (6 weeks and 6 months):** using the Malnutrition Screening Tool [53]. This is a brief screening tool to assess nutritional status, with smaller scores indicating better nutritional status.**Health care resource utilization and costs (baseline and 6 months):** Health care resource utilization will be assessed through financial micro-costing databases. A modified health resource utilization questionnaire [54] will be administered at the final follow up visit to identify patient out-of-pocket expenses and indirect carer costs.

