### Data analysis

We will evaluate the effectiveness of the EASE initiative implementation by comparing between-site mean changes in each outcome in the cohort of patients hospitalized from the baseline cohort (defined as “pre-EASE”) to those hospitalized after implementation (defined as “post-EASE”).

Initially, exploratory data analysis will be performed on each major variable, including calculation of means, medians, proportions, and measures of central tendency. Baseline variables pre-EASE and post-EASE will be compared between sites using *X*^2^ tests for categorical variables, Student T-tests for normally distributed continuous variables, and the Wilcoxon rank sum test for non-normally distributed variables.

Secondly, within-site mean change scores will be computed for the composite primary outcome (difference of proportions) and the overall covariate-adjusted between-site pre-post difference (‘difference of differences’) will be the dependent variable analyzed using generalized linear mixed model procedures and will include adjustment for clustering by study site and operating surgeon. The regression model will be constructed using recommended techniques and assessment of model assumptions (including tests of normality, tests of colinearity and log-transformation of non-normally distributed continuous variables) will be performed as necessary. Additional adjustment for baseline age, sex, BMI, ethnicity, blood pressure, heart rate, respiratory rate, haemoglobin, creatinine, admitting diagnosis, medical comorbidities, operative procedure, Rockwood clinical frailty score, Charlson comorbidity index, American Society of Anaesthesiologists class, baseline month of enrolment, and/or baseline place of residence will be performed. Secondary endpoints will be analyzed as ‘difference of differences’ in a manner similar to that outlined for the primary outcome.

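### The plan promises a cost per QALY gained but defines it, site by site, as a cost difference over a QALY level, with neither term netted against the control site's change

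*Protocol article*

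**What the plan says.** The third objective in the protocol article (Aim & objectives) is incremental: "Determine the incremental cost and cost-effectiveness of the EASE initiatives".

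The cost paragraph of the Data analysis section names the target: "A cost per quality adjusted life year (QALY) gained will also be calculated". The next sentence says how it will be formed: "The mean cost difference in each site will be divided by the QALYs achieved in each site". The one after that says what a QALY is here: "QALYs will be calculated using the utility values measured by the EQ-5D and the length of life of each patient".

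Earlier in the same paragraph, intervention cost is added to post-EASE costs, and costs are contrasted across hospitals: "All costs pre-EASE and post-EASE will be compared between sites" and "The difference in costs between sites will be calculated and compared". No matching contrast is stated for QALYs.

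The preceding part of the section sets a general rule: "Secondary endpoints will be analyzed as ‘difference of differences’ in a manner similar to that outlined for the primary outcome". The Outcomes section lists quality of life and health care costs among the secondary outcomes.

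**The concern.** A cost per QALY gained needs a difference in both terms: extra cost over extra QALYs. The stated formula has a difference on top and, on its plain reading, a level underneath. Such a ratio is finite and positive whenever cost rises, whether patients gain QALYs, lose them or stay the same.

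The second problem does not depend on the first. The ratio is formed separately at each hospital. At the intervention site it therefore absorbs any change over time that would have occurred without EASE. At the control site it describes a hospital where EASE is not introduced. The plan itself expects change without EASE: the Sample size calculation section assumes a 5 % decline in the primary outcome at the control site, against 15 % at the intervention site. The concurrent control is there to remove such change, and the ratio does not use it for that.

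At stake is the economic objective, one of three. Followed to the letter, it would be answered with a number that does not measure cost-effectiveness and could make a programme that loses QALYs look inexpensive.

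**Working it through.** The documents contain no cost, QALY or cost-effectiveness figure, so there is nothing to reproduce. The check is algebraic, followed by an illustration in which **every input is assumed**.

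**Formulas.** C is mean cost per patient and Q is mean QALYs per patient. The cost difference in a site is read as post minus pre, and the QALYs achieved as those of the post-EASE cohort.

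- Stated ratio, per site: (C_post − C_pre) / Q_post
- Ratio that matches the objective and the design: [(C_post − C_pre) at intervention − (C_post − C_pre) at control] / [(Q_post − Q_pre) at intervention − (Q_post − Q_pre) at control]

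Q_pre appears nowhere in the stated ratio, so the ratio cannot show whether QALYs rose or fell.

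**Illustration 1: the denominator.** Intervention-site cost rises from 20,000 to 21,000, control-site cost and QALYs do not change, and the pre-EASE QALY is 0.35 at both sites. The net cost is 1,000.

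| Net QALY change | Post-EASE QALY | Stated ratio, intervention site | Incremental ratio |
|---|---|---|---|
| +0.04 | 0.39 | 1,000/0.39 = 2,564 | 1,000/0.04 = 25,000 |
| +0.01 | 0.36 | 1,000/0.36 = 2,778 | 1,000/0.01 = 100,000 |
| 0 | 0.35 | 1,000/0.35 = 2,857 | undefined (no QALY gained) |
| −0.01 | 0.34 | 1,000/0.34 = 2,941 | dominated (dearer, fewer QALYs) |

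From the first row to the last the stated ratio moves by 2,941/2,564 − 1, about 15 %. The incremental ratio quadruples between the first two rows and then ceases to be a price at all.

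**Illustration 2: netting, with change at both sites.** Costs go from 20,000 to 21,000 at the intervention site and from 20,000 to 20,500 at control. QALYs go from 0.35 to 0.37 and from 0.35 to 0.355.

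- Stated ratios: 1,000/0.37 = 2,703 (intervention) and 500/0.355 = 1,408 (control)
- Correcting only the denominator, still within the intervention site: 1,000/0.02 = 50,000
- Correcting both: (1,000 − 500)/(0.020 − 0.005) = 500/0.015 = 33,333 per QALY gained

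Changing the denominator alone is therefore not enough. The within-site figure of 50,000 still counts the change that also occurred at control.

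**Illustration 3: a net saving.** Keep the QALYs of illustration 2, but let cost rise by 500 at the intervention site and by 1,000 at control. The stated ratio at the intervention site is 500/0.37 = 1,351, an apparent positive price. Net of control, EASE saves 500 and gains 0.015 QALY, so it is both cheaper and better.

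**The case against.** The strongest defence is that this is loose wording in a condensed article. The sentence before the formula says QALYs gained, the objective says incremental, and the general rule nets secondary endpoints against control. On that view, QALYs achieved means the QALY change, and the team would calculate the right thing. This cannot be excluded. But the definition that follows builds QALYs as levels, and no QALY contrast is stated anywhere. Even if the charitable reading is granted, a ratio formed in each site still departs from the netting rule. The sentence needs rewriting on either reading. It is a stated formula, not a detail left to a fuller document.

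Some stronger readings are tempting, and the documents do not support them:

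- *That the control site is ignored.* It is not: the ratio is formed at both sites, and costs are compared between them. The gap is that this contrast is not carried into either term of the ratio.
- *That the stated ratio is unaffected by EASE.* The cost effect enters the numerator, and the post-EASE QALY level enters the denominator. The ratio responds to a QALY effect, but weakly.
- *That the two site ratios will be subtracted from each other.* The plan does not say so.
- *That the economic result is bound to be wrong.* This follows only if the formula is applied to the letter over the target named just before it.
- *That the lack of a bootstrap interval, a net-benefit analysis or a stated horizon is part of the error.* Such details may sit in documents not shown and are not counted here.

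**Conclusion.** The formula is wrong as written. It contradicts the target named in the preceding sentence, the incremental objective, and the plan's own rule for secondary endpoints. The conflict in the denominator rests on the plain reading of the QALY definition. The failure to net against control holds on either reading.

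The size depends on assumed inputs. With a net cost of 1,000 and a pre-EASE QALY of 0.35, the stated ratio lies between about 2,560 and 2,940 for QALY changes from +0.04 to −0.01, where the proper ratio runs from 25,000 to dominated. Other inputs would change these figures, but not the fact that the stated ratio lacks the pre-EASE QALY term.

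The effect is confined to the secondary economic objective. The primary composite outcome, its model and the sample size are untouched.

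**What to change.** Delete the per-site ratio and define one ratio in its place:

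- **Numerator:** pre-post change in mean cost at the intervention site, with intervention cost included as already planned, minus the pre-post change at the control site.
- **Denominator:** pre-post change in mean QALYs at the intervention site, minus the pre-post change at the control site.
- **Period:** costs and QALYs counted over the same stated period.

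This takes about two sentences and no new data, because costs and EQ-5D are already collected in all four cohorts, and it can be done before analysis. It corrects the formula only. EQ-5D comes from follow-up interviews ("Quality of life and health status (6 weeks and 6 months") that require consent, while in-hospital data come from chart review under a consent exemption. How patients without EQ-5D enter the denominator is a separate question that the rewording does not settle.
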